### The educational intervention

The GET is a clinical educational instrument that has been developed by a team at UNSW Medicine, Australia. It is structured to facilitate a two stage process of engagement. Each stage (requiring approx. 30–45 mins) is designed to fit within existing workshop style GP training sessions. The two stages are based on two instruments (A&B) that have been designed to guide clinicians’ engagement with hypertension guidelines and the key decision points in managing hypertension. The GET will be supplemented by a final panel discussion with experts (experienced general practitioners and a cardiologist) which will enable participants to discuss any concerns and clarify any issues that arises out of their engagement with the GET. This discussion, drawing on participant experiences of the usefulness of the guidelines, also aims to develop recommendations to enhance the usability of the existing guidelines.

The first stage instrument (A) is based on a straightforward hypertension patient presentation, devoid of any complicating contextual factors. This stage provides a framework for clinicians to critically evaluate their decisions in relation to such a hypertension presentation. This stage will focus clinicians on the ‘key decision points’ relevant to the ideal management of such an uncomplicated patient presentation, and will facilitate clinicians’ engagement with hypertension guidelines.

The second stage instrument (B) will be based on a typical patient presentation in a general practice setting, including contextual influences related to patients, practice limitations and time pressure considerations. This stage will provide a guide to the key decision points that need to be considered by the clinicians, with a framework to identify and articulate the reasons for their decisions in relation to the key decision points. This process will also provide a mechanism for clinicians to identify specific contextual factors that influence their decisions.

It is envisaged that this two stage process will not only enhance clinician engagement with hypertension guidelines, but will also enhance their clinical decision making skills.

The second stage instrument (B) also encourages clinicians to reflect on contextual issues particular to the management of hypertension in general practice, and allows them to suggest potential modifications to the guidelines. This is an important contribution to the process of continuously improving the quality of clinical practice guidelines, in order to meet conditions or contexts which might have been overlooked or have become outdated.

The final expert panel discussion will provide an opportunity for these suggestions to be discussed with relevant experts and peers, in order to develop evidence-based, contextually appropriate, consensus guidelines. This will address a commonly identified issue that impacts on the uptake of guidelines: the perceived ‘top-down’ nature of guidelines and accompanying interventions to promote their use, and the limited involvement of end-user clinicians in the process of guideline development [17-19].

The GET will be reviewed by senior GPs and will be trialled on GPs and GP trainees (who have progressed beyond the participants’ stage of training). Feedback from this process will be systematically collected and used to inform further refinements if required.

### Measures

The script concordance test (SCT) is a test designed to assess examinees’ organisation of knowledge for application in clinical decisions [15]. The organisation of knowledge is named a script. This written test is based on authentic clinical scenarios that form the basis for test items. The test items are categorised as diagnostic, investigative or treatment options and examinees are required to rate their agreement with the provided response options based on a combination of clinical information that is provided [15]. While it is a relatively new assessment method, the SCT is well established in the medical education literature as a tool with good psychometric properties and good face validity for assessment of clinical decision-making competence. It is expected that the SCT will enable the evaluation of the impact of the GET on developing clinical reasoning skills.

Prior to commencement of the study, the SCT items will be reviewed by the project team that includes experienced GPs and medical educators. An SCT scoring panel of experienced GPs will be established to ensure scoring that is relevant to the GP trainee context.

Participating registrars will also be invited to participate in semi-structured qualitative interviews that will take about 20–30 minutes, to obtain their views on the effectiveness and feasibility of GET.

Written informed consent will be obtained from participants, using two ‘Participant Information & Consent Forms’ approved by the Human Research Ethics Panel of UNSW Australia (Approval ID: 2014-7-26). Informed written consent will thus be obtained for both the survey stage and the interview stage of the study.

### Statistical analysis

The main analyses in this study will employ Analysis of Variance (ANOVA). (a) Factorial ANOVA will be used to compare the two groups at Time Point 1 and identify possible differences on SCT scores across groups; (b) One-way repeated measure ANOVA will be used to measure the impact of the intervention by comparing differences in SCT scores within individuals and across groups between Time Point 1–2 and between Time Point 2–3. This analysis is appropriate as it allows identifying the source for the change in the SCT scores (intervention, initial level of competence or errors [20], and testing the hypothesis that the change in the SCT was made by the intervention. We set up a significance level of p < .05 to demonstrate that the intervention was successful.

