## Methods and design

### Study design

This is a non-randomised, delayed intervention study design. The study is not randomised since the educational intervention will be administered in groups and randomising groups will require unrealistic sample size. However, using repeated measures and a delayed intervention design provides an optimal solution without compromising the study quality. Such a design is preferable for evaluation of the educational intervention since all participants receive the intervention and the design enables measure of progress across and within groups, including control for possible (although unlikely) differences between groups at the starting time.

Clinicians participating in this study will be recruited from a population of general practice registrars who are undergoing GPTerm1 or GPTerm2 stages of training at GP Synergy (a major provider of general practice training in Australia), at two training sites. Participants from site A will be the ‘early intervention group’ while the group at site B will be the ‘delayed intervention group’. The two interventions will be identical and will differ only by the time of implementation. Participants will undergo evaluations of clinical reasoning (based on the Script Concordance Test (SCT) [15] upon commencement of project (Time Point 1: before the early intervention), immediately after the early intervention and before the delayed intervention starts (Time Point 2), and at the end of the delayed intervention (Time Point 3).

The impact of the intervention will be measured by comparing the progress each group makes (changes in SCT scores) over each intervention period.

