### Sample size

Two systematic reviews suggest that the effect size on SCT between resident doctors and expert doctors ranged 0–3.2; typically around 1 and the effect of educational interventions such as Educational meetings/interactive educational sessions was d > 1 [16,17]. Based on those studies, we expect that the intervention will yield an effect size of d ≥ 1.0 measured by the differences in the SCT results between the intervention and the control groups between Time Point 1 and Time Point 2. A similar increase is expected for the delayed intervention group between Time Point 2 and Time Point 3. Therefore, a sample size of 34 clinicians (17 intervention & 17 control) will have 80% power to detect an effect size of d = 1 (one sd.) with an alpha of 0.05 (two sides) [18].

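### With 17 per group the Time Point 1 ANOVA cannot show that the two sites are comparable, and the outcome model as named has no term for training stage or initial SCT

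*Protocol article*

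**What the plan says.** The Study design section is open about allocation: "This is a non-randomised, delayed intervention study design". Group is the same thing as site: "Participants from site A will be the ‘early intervention group’ while the group at site B will be the ‘delayed intervention group". Recruits are "general practice registrars who are undergoing GPTerm1 or GPTerm2 stages of training", and no balancing of the two stages across sites is described. The same section lists among the merits of the design "including control for possible (although unlikely) differences between groups at the starting time".

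The Statistical analysis section has two steps.

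- Step (a): "Factorial ANOVA will be used to compare the two groups at Time Point 1 and identify possible differences on SCT scores across groups". It names no factor other than group, no significance level for this test, no size of imbalance that would matter, and no consequence of the result.
- Step (b): a one-way repeated measures ANOVA of SCT differences, within persons and across groups, over Time Points 1–2 and 2–3. The section says that this analysis can attribute change in SCT to the intervention, to initial competence or to error. It makes p < .05 the mark of success.

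Training stage appears in the description of recruits and nowhere in the analysis.

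**The concern.** When groups are formed by site, nothing in the design makes them alike at the start, and the article gives no reason for calling a difference unlikely. The only stated check is a test of Time Point 1 scores in a study sized to detect an effect of 1 SD. A reader who sees a non-significant result would naturally take it as support for comparability, and a test of this size cannot give that support.

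The second half concerns what step (b) can do about a difference that does exist. It is credited with separating initial competence from the intervention, but the model as named has no term through which initial SCT or training stage could act. If GPTerm1 and GPTerm2 registrars progress at different rates and the sites differ in their mix, or if one site starts high or low by chance and drifts back, part of that movement is counted as effect of the GET.

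**Working it through.** **Inputs.** 17 per group (Sample size section: "a sample size of 34 clinicians (17 intervention & 17 control) will have 80% power to detect an effect size of d = 1"). The same section has "with an alpha of 0.05 (two sides"; no level is stated for the Time Point 1 test, so two-sided 0.05 is assumed there too. SCT is in SD units. Step (a) is treated as a two-group comparison; a second factor that explained variance would raise the power somewhat.

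**Step 1: reproduce the plan's figure.** For a two-sample t test, df = 2n − 2 and the noncentrality is d√(n/2). With n = 17 and d = 1, df = 32, the noncentrality is √8.5 = 2.92 and the critical t is 2.037. Power is 80.7%. With 16 per group it is 78.1%, so 17 is the smallest group size that reaches 80%. The stated sample size reproduces.

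**Step 2: the same test applied at Time Point 1.**

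| True imbalance (SD) | Detected | Missed |
|---|---|---|
| 0.2 | 8.7% | 91.3% |
| 0.3 | 13.6% | 86.4% |
| 0.5 | 29.3% | 70.7% |
| 0.8 | 61.9% | 38.1% |
| 1.0 | 80.7% | 19.3% |

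**Step 3: what a non-significant result leaves open.** The smallest significant observed difference is 2.037 × √(2/17) = 2.037 × 0.343 = 0.70 SD. This is also the half-width of the 95% confidence interval. Even an observed difference of zero leaves true differences of up to about 0.70 SD either way compatible with the data. Power reaches 50% only at a true imbalance of about 0.69 SD.

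**Step 4: training stage (illustration; the documents give neither a stage effect nor a stage mix).** Baseline imbalance = stage difference in SCT × difference in stage mix. If the stages differ by 0.5 to 1.0 SD and the mix differs by 30 percentage points, the imbalance is 0.5 × 0.30 = 0.15 to 1.0 × 0.30 = 0.30 SD. The test finds this 7.1% to 13.6% of the time. Within-person change removes this imbalance if both stages progress alike. If one stage gains h SD more over a period, the group comparison for that period is shifted by 0.30 × h.

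**Step 5: regression to the mean (illustration; the documents give no correlation r between time points).** Take a baseline difference of 0.5 SD.

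- If it is transient, the expected later difference is r × 0.5, so the change-score comparison is shifted by (1 − r) × 0.5. For r = 0.4, 0.6 and 0.8 that is 0.30, 0.20 and 0.10 SD.
- If it is stable, the change-score comparison is not shifted. A model adjusted for Time Point 1 SCT with slope r is then off by 0.5 − r × 0.5 = (1 − r) × 0.5, the same amounts, unless stage explains the difference.

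The two analyses rest on opposite assumptions, and the Time Point 1 test does not tell which holds.

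**Step 6: claim against model.** A one-way repeated measures model has one factor. Comparing across groups already needs a second. Attributing change to initial competence needs a term for it, and none is named.

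**The case against.** The strongest reply is that the baseline test is not the safeguard. Step (b) analyses change within persons, so any constant difference between sites drops out, including a stable gap between GPTerm1 and GPTerm2. That is right. A reader might infer that the analysis adjusts for nothing; the text does not support this.

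A reader might also take step (a) as a gate that decides the model or declares the sites comparable. The article states no such rule, and nothing makes step (b) depend on the result. The objection is to what the test can show.

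It is tempting to size the stage effect from the roughly 1 SD in the Sample size section. That figure compares resident doctors with experts, over a range of 0 to 3.2. Both GPTerm stages are trainees, and no SCT gap between them is given. Nor can 0.2 SD be read as the bias of this study: it needs a transient 0.5 SD imbalance and r = 0.6, and a difference in stage mix is not transient.

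The delayed design helps too. With roles reversed over Time Points 2–3, a steady difference in progress between sites would push the two comparisons in opposite directions. This is a partial check on differing growth, provided that both periods are read together.

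Finally, a condensed article may leave covariates to a fuller plan, and a factorial ANOVA implies a further factor in step (a), which could be stage. Silence alone would therefore be no finding. But the model for step (b) is stated, its name leaves no place for stage or initial SCT, and it is credited with identifying initial competence. That mismatch is in the text.

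**Conclusion.** The point holds in a limited form. A non-significant Time Point 1 result with 17 per group cannot show that two non-randomised sites are comparable: power is 29% at 0.5 SD, and the confidence interval reaches about 0.70 SD either side. This assumes a two-sided 0.05 level. Whether 0.5 SD matters is a judgement, because the article sets no threshold; an imbalance of 1 SD would be found 81% of the time.

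The outcome model removes a constant baseline difference. As named, it does not address different growth by training stage or regression to the mean, and it cannot deliver the stated separation of initial competence from the intervention. The documents do not allow the resulting bias to be sized; the figures in steps 4 and 5 of the working are illustrations only.

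This is a cheap improvement to the analysis. It does not invalidate the design.

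**What to change.** 1. Replace reliance on the Time Point 1 p-value with a description by group: mean SCT, the difference with its 95% confidence interval, and the numbers in GPTerm1 and GPTerm2. In the Study design section, delete the parenthetical that calls starting differences unlikely.
2. Replace the one-way model with a repeated measures model containing group, time, group by time, GPTerm and GPTerm by time, fitted whatever the baseline comparison shows.
3. Pre-specify one sensitivity analysis: Time Point 2 SCT regressed on group, Time Point 1 SCT and GPTerm. Report both estimates with confidence intervals. State that change-score and baseline-adjusted estimates rest on different assumptions when groups differ at the start, so some divergence is expected then and is not in itself evidence against an effect.
4. Limit the statement about initial competence to what the revised models estimate.

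Cost: about three degrees of freedom with 34 participants (one for GPTerm, two for GPTerm by time over three time points) and one extra model. SCT at Time Point 1 is already measured and training stage defines who is recruited, so no new data are needed. None of this removes the remaining confounding of group with site, which should be stated as a limitation.

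### The one-way repeated-measures ANOVA named as the test of impact has no group factor, so it contradicts the across-group comparison in its own sentence and the contrast that sizes the study

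*Protocol article*

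**What the plan says.** The Statistical analysis section has two parts. In part (a), "Factorial ANOVA will be used to compare the two groups at Time Point 1", so the group comparison there is confined to baseline. Part (b) carries the effect of GET: "One-way repeated measure ANOVA will be used to measure the impact of the intervention by comparing differences in SCT scores". The sentence continues that this is done "within individuals and across groups between Time Point 1–2 and between Time Point 2–3".

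The section then defends the choice, saying that it allows "identifying the source for the change in the SCT scores (intervention, initial level of competence or errors"), and ties success to the result: "We set up a significance level of p < .05 to demonstrate that the intervention was successful".

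Two other sections bear on this:

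- **Study design:** "This is a non-randomised, delayed intervention study design". Site A receives GET early and site B later. Impact is to be judged by comparing how far each group progresses.
- **Sample size:** the expected effect of d = 1 is "measured by the differences in the SCT results between the intervention and the control groups between Time Point 1 and Time Point 2", with 17 participants per group.

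**The concern.** One-way means one factor, and in a repeated-measures ANOVA that factor is time. Over two time points the test is a paired t test (F equals t squared). It asks whether mean SCT score moved, and it holds no term for early versus delayed group. The words that follow in the same sentence ask for something this model cannot deliver.

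The participants are registrars in active training who sit the SCT three times, so scores could rise without GET. The listed sources of change are the intervention, initial competence and error. Retest and ordinary training gain are absent, and in the named model they cannot be told apart from an intervention effect.

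What is at stake is the main claim of the study. An analyst who follows the test name could report a rise over time as proof that GET worked, even if the untreated site rose by the same amount. An analyst who follows the rest of the sentence would fit a different model. Both could say they kept to the plan.

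**Working it through.** **Inputs from the protocol article.** Sample size: 17 per group, d = 1, two-sided alpha 0.05, power 80%. Statistical analysis: one-way repeated-measures ANOVA, success at p < .05.

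**Inputs assumed, because the document gives none.** A retest or training gain g, the same at both sites, of 0, 0.2, 0.3 or 0.5 score SDs per interval. A correlation r between Time Points 1 and 2 of 0.5, 0.7 or 0.8.

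**Step 1. Reproduce the sample size.** For two independent groups, the normal approximation gives n per group = 2(1.960 + 0.842)² / d² = 2 × 7.85 / 1 = 15.7, so 16. The exact two-sample t calculation gives 16.71, so 17 per group, with 80.7% power. The stated 34 is therefore correct, and it is a calculation for a between-group test.

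**Step 2. Set the parts of the plan side by side.**

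| Place | Contrast described | Available in a one-way repeated-measures ANOVA? |
|---|---|---|
| Study design | Progress of one group against the other | No |
| Sample size | Intervention versus control, Time Point 1 to 2 | No |
| Statistical analysis (b), description | Within individuals | Yes |
| Statistical analysis (b), description | Across groups | No |
| Statistical analysis, justification | Intervention as source of change | No, only time |

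**Step 3. Rejection rate of the named test when GET does nothing.** With score SD set to 1, the SD of the change is √(2(1 − r)). The standardised change is dz = g / √(2(1 − r)), and the noncentrality is dz × √n with n − 1 degrees of freedom.

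Example: g = 0.3, r = 0.7, n = 17. The SD of change is √0.6 = 0.775, dz = 0.3 / 0.775 = 0.387, and the noncentrality is 0.387 × 4.123 = 1.60. The two-sided rejection rate is 32.4%. A simulation of 20,000 trials also gave 32.4%.

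Percentage of trials with p < .05 in one group of 17, no GET effect:

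| r | g = 0 | g = 0.2 | g = 0.3 | g = 0.5 |
|---|---|---|---|---|
| 0.5 | 5 | 12.1 | 21.4 | 49.1 |
| 0.7 | 5 | 17.0 | 32.4 | 70.5 |
| 0.8 | 5 | 23.2 | 45.2 | 86.4 |

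**Step 4. The same setting with a group-by-time test.** Over two time points this is a two-sample t test on the change scores. If both sites gain g, the expected difference in change is (GET effect + g) − g = GET effect, so the shared gain cancels. Simulation at g = 0.3 and r = 0.7 gave 4.8% rejection. If one site gains more than the other for reasons unrelated to GET, that excess does not cancel and is added to the estimate.

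**Step 5. Effect on the sample size.** If d = 1 is in units of the SD of change, 17 per group keeps 80.7% power. If it is in units of the raw score SD, the effect on the change scale is 1 / √(2(1 − r)), and power is 51.6%, 80.7%, 95.4% or 99.4% for r of 0, 0.5, 0.7 or 0.8.

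**The case against.** The strongest reply is that only the word one-way is at fault. The sentence goes on to include a comparison across groups, Study design describes the same comparison, and Sample size is built on it. A condensed article may also leave model terms to a fuller document that is not shown.

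Much of this stands. A reader might infer that the plan ignores its control group, or that the delayed group plays no part in the test. The documents do not support that: three sections give that group a role, and the inference follows only if the test name is obeyed and its description set aside. Nor does any section propose one time test on all 34 participants together, so rejection rates for such a test are not evidence against this plan. The gain is conjecture too. The article does not say how far apart the time points are or whether SCT items are reused, and with no gain the named test rejects at 5%.

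What does not stand is treating the matter as detail left out. The article names a specific test, says "This analysis is appropriate as it allows identifying the source for the change in the SCT scores", and attaches the success criterion to it. That is a wrong statement about the chosen model, and the words about comparing across groups turn it into a contradiction without resolving it.

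A reader might also infer that a group-by-time test would isolate GET from all ordinary training gain. It would not. The study has one site per arm and no randomisation, so only gains common to both sites are removed.

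**Conclusion.** The main analysis is wrongly named. The intended between-group contrast can be recovered from the rest of the article, and the sample size matches it, but the test that decides success does not contain it. The justification credits that test with an attribution it cannot make.

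The 12% to 86% range is conditional. It applies if the test is run literally within one group of 17, GET has no effect, and the gain and correlation lie in the assumed ranges. It shows how far the conclusion could depend on which half of the sentence the analyst follows. It does not forecast what this study will report. The contradiction itself rests on no assumed figure.

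**What to change.** In part (b), replace the one-way test with a mixed ANOVA of group (early or delayed) by time. The primary test is the group-by-time interaction over Time Points 1 to 2, or equivalently a between-group comparison of the change over that interval, reported with its 95% confidence interval. Attach the p < .05 criterion to that test.

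Keep the delayed group's change over Time Points 2 to 3 as supporting evidence. The early group has already been treated by then and is not an untreated control for that interval.

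Replace the source-of-change claim with a statement that the interaction removes only gains common to both sites. Say that with one site per arm and no randomisation, site-specific gains remain confounded with GET.

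The cost is a reworded analysis paragraph, with no new data or participants. The total of 34 can stay if d = 1 refers to the SD of change; the Sample size section should say which SD is meant.

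### The planned one-way repeated-measures ANOVA does not separate a GET effect from ordinary learning, and the only sized contrast is confounded with site; naming group-by-time contrasts would be a cheap improvement

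*Protocol article*

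**What the plan says.** All places are in the protocol article, under Methods and design.

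- **Study design.** Allocation is by training site and is not randomised: "Participants from site A will be the ‘early intervention group’ while the group at site B will be the ‘delayed intervention group". The SCT is taken at the start, then "immediately after the early intervention and before the delayed intervention starts (Time Point 2), and at the end of the delayed intervention (Time Point 3". Impact is to be judged by "comparing the progress each group makes (changes in SCT scores) over each intervention period". The design is said to allow progress to be measured both across and within groups, "including control for possible (although unlikely) differences between groups at the starting time".
- **Sample size.** The 17 + 17 registrars are sized for d = 1 on the "differences in the SCT results between the intervention and the control groups between Time Point 1 and Time Point 2". For the other interval the section adds: "A similar increase is expected for the delayed intervention group between Time Point 2 and Time Point 3".
- **Statistical analysis.** Part (a) compares the groups at Time Point 1. Part (b) is a one-way repeated-measures ANOVA "comparing differences in SCT scores within individuals and across groups between Time Point 1–2 and between Time Point 2–3". The section says this can attribute a change in score to the intervention, to initial competence or to error. Success is a p-value below .05, with no contrast named.

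**The concern.** Participants are registrars in active training who sit the same kind of test three times, so some gain without GET is to be expected. The sources of change listed in Statistical analysis leave out ordinary learning, retest gain and site.

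Two consequences follow. First, the sized contrast compares two sites over one interval. If registrars at site A would have gained more than those at site B anyway, the excess is counted as a GET effect. Part (a) looks only at starting level, and equal starting levels say nothing about equal rates of gain. Second, a rise in the delayed group from Time Point 2 to 3 is expected whether or not GET works, unless it is judged against that group's own rise while waiting.

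The three-time-point design collects data that help with both problems. The stated one-way analysis does not isolate the contrasts that would use them, and the success criterion does not say which comparison it refers to.

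**Working it through.** **1. The plan's own figure.** Inputs from Sample size: d = 1, two-sided alpha 0.05, 80% power, 17 + 17. A two-sample t-test needs 16.7 per group, so 17. At 17 per group the non-centrality is 1/√(2/17) = 2.92 on 32 df, and power is 80.7%. The stated 34 is reproduced.

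**2. What each contrast estimates.** Let e be the GET effect and sA1, sA2, sB1, sB2 the ordinary gains by site and interval. Suppose site A keeps its GET gain.

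| Contrast | Estimates |
|---|---|
| Main: A minus B, Time Points 1–2 | e + (sA1 − sB1) |
| B minus A, Time Points 2–3 | e + (sB2 − sA2) |
| Raw rise in B, Time Points 2–3 | e + sB2 |
| (i) B: (TP3 − TP2) − (TP2 − TP1) | e + (sB2 − sB1) |
| (ii) Average of the first two rows | e + [(sA1 − sA2) + (sB2 − sB1)]/2 |

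If the site difference is a constant s = sA − sB, the first row gives e + s, the second e − s, and their average e. Contrast (i) has no between-site term, but it needs sB1 = sB2. If site A loses an amount δ of its gain by Time Point 3, the second row rises by δ and (ii) by δ/2.

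**3. Size of the site bias in the main contrast.** The documents give no value of s, so the values here are assumed. With e = 0, 17 per group and s in SDs of change, the non-centrality is s/√(2/17).

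- s = 0.3: 0.87, significant in favour of GET in 13.3% of trials.
- s = 0.5: 1.46, in 29.3%.
- s = 0: 2.5%, the nominal rate.

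At s = 0.5 the Time Point 2–3 between-group contrast would falsely favour GET in only 0.04% of trials, because the bias changes sign.

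**4. The raw rise in the delayed group.** With e = 0 and an assumed ordinary gain of 0.3 or 0.5 SD of change, a paired test of Time Points 2–3 (n = 17, non-centrality 0.3√17 = 1.24 or 0.5√17 = 2.06, 16 df) favours GET in 21% or 49% of trials.

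**5. What a one-way test does.** Simulation for site B alone: 5,000 runs, n = 17, between-time correlation 0.5 (assumed), no GET effect, steady learning per interval in SDs of scores.

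| Learning per interval | One-way ANOVA rejects | Contrast (i) rejects |
|---|---|---|
| 0 | 5.1% | 5.3% |
| 0.25 | 40% | 5.3% |
| 0.5 | 95% | 5.2% |

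**6. Precision of the supportive contrasts.** Under compound symmetry with within-person error variance v, a change has variance 2v and contrast (i) has (1 + 4 + 1)v = 6v. The SD ratio is √3. An effect of 1 SD of change becomes 1/√3 = 0.577, and power at n = 17 is 61%. If d = 1 is in SDs of scores, the standardised effect is 1/√(6(1 − r)), and power is 47%, 61% or 82% for an assumed r of 0.3, 0.5 or 0.7.

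For (ii), the variance is (6v + 6v)/4 = 3v divided by 17. In SDs of change (2v = 1) the standard error is √(1.5/17) = 0.297. The non-centrality at d = 1 is 3.37 and power is about 90%, if site A keeps its gain.

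**7. Overlap of (i) with the main contrast.** Both subtract site B's waiting-period change. Per 1/n, the variances are 4v and 6v and the covariance is 2v + v = 3v, so the correlation is 3/√24 = 0.61. The difference between the two estimates has variance (4 + 6 − 6)v/17, which is a standard error of √(2/17) = 0.34 SD of change.

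**The case against.** The strongest reply is that the plan already announces a comparison within individuals and across groups over both intervals. That can be read to include the delayed group's GET-period gain against its own waiting-period gain, and a condensed article may leave the exact contrasts to a fuller document. This stands in part. A reader might infer that the plan never uses the waiting-period gain, and the text does not support that: it leaves the contrast unnamed. What remains is what the article does state: a one-way test that does not isolate the contrast, a claim that this test identifies the source of change, and a p-value criterion attached to nothing.

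A reader might also infer that contrast (i) is the only one free of site confounding. It is not. The plan also covers the between-group comparison over Time Points 2–3, and averaging the two period contrasts cancels a constant site difference, with better power.

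Nor would agreement between (i) and the main contrast prove an effect independent of site. Both contain site B's waiting-period change, so a poor waiting period inflates both.

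Two further points hold. Sample size only voices an expectation for the delayed group and sets no success rule on it. Both sites belong to one training provider and draw on the same training stages, which makes a large site difference in learning less likely but does not exclude it.

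**Conclusion.** The point holds as a cheap improvement to the analysis section. It does not show that the trial's data cannot answer the question. As written, the only sized contrast carries any site difference in ordinary learning in full, the Time Point 1 comparison cannot reveal it, and the one-way ANOVA can reject on steady learning alone. The 13% and 29% rates rest on assumed site differences of 0.3 and 0.5 SD of change, and the documents give no estimate of either. The power figures for (i) and (ii) assume compound symmetry, and the figures of 47% to 82% for (i) also assume a between-time correlation. No single contrast removes every bias: (i) needs equal ordinary gain in the delayed group's two intervals, and (ii) needs a constant site difference and retention of the gain in the early group.

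**What to change.** **Statistical analysis.** Replace the one-way analysis with a group-by-time repeated-measures model using all three time points. Name the early-versus-delayed difference in change over Time Points 1–2 as the main contrast and tie p < .05 to it. Report two supportive estimates with 95% CIs:

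- (i) in the delayed group, (TP3 − TP2) − (TP2 − TP1), stating that it assumes equal ordinary gain in both intervals;
- (ii) the average of the two between-group period contrasts, stating that it cancels a constant site difference and assumes the early group keeps its gain.

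State that (i) shares the delayed group's waiting-period change with the main contrast, so agreement is supportive and not independent proof. Do not require the estimates to be of similar size: with a standard error of 0.34 SD of change for their difference, sizeable gaps will arise by chance.

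**Sample size.** Reword the expectation for the delayed group over Time Points 2–3 as *an increase over and above its own Time Point 1–2 change*.

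**Cost.** No new data or visits are needed, only a change of model and two extra reported estimates. The main drawback is that (i) is noisy, with about 61% power at d = 1 SD of change against 81% for the main contrast. That is a reason to keep it supportive.
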